## Abstract

**Background:**

An estimated 17,000 patients are treated annually in the UK with radical radiotherapy (RT) for pelvic cancer. New treatment approaches in RT have increased survivorship and changed the subjective toxicity profile for patients who experience acute and long-term pelvic-related adverse events (AE). Multi-disciplinary follow-up creates difficulty for monitoring and responding to these events during treatment and beyond. Originally developed for use in systemic oncology therapy eRAPID (electronic patient self-Reporting of Adverse-events: Patient Information and aDvice) is an online system for patients to report AEs from home. eRAPID enables patient data to be integrated into the electronic patient records for use in clinical practice, provides patient management advice for mild and moderate AE and advice to contact the hospital for severe AE. The system has now been developed for pelvic RT patients, and we aim to test the intervention in a pilot study with staff and patients to inform a future randomised controlled trial (RCT).

**Methods:**

Eligible patients are those attending St James’s University hospital cancer centre and The Christie Hospital Manchester undergoing pelvic radiotherapy+/−chemotherapy/hormonotherapy for prostate, lower gastrointestinal and gynaecological cancers. A prospective 1:1 randomised (intervention or usual care) parallel group design with repeated measures and mixed methods will be employed. We aim to recruit 168 patients following recommendations for sample size estimates for pilot studies. Participants using eRAPID will report AE (at least weekly) from home weekly for 6 weeks and 6 weeks post-treatment (12-week total) then at 18 and 24 weeks. Hospital staff will review eRAPID reports and use information during consultations. Notifications will be sent to the relevant clinical team when severe symptoms are reported. We will measure patient-reported outcomes using validated questionnaires (Functional Assessment in Cancer Therapy Scale-General (FACT-G), European Organisation for Research and Treatment of Cancer Core Quality of Life questionnaire (EORTC-QLQ-C30), process of care impact (hospital records of patient contacts and admissions) and economic variables (EQ5D-5L, patient use of resources)). Staff and patient experiences will be explored via semi-structured interviews.

**Discussion:**

The objectives are to establish feasibility, recruitment, integrity of the system and attrition rates, determine effect sizes and aid selection of the primary outcome measure for a future RCT. We will also refine the intervention by exploring staff and patient views. The overall goal of this complex intervention is to improve the safe delivery of cancer treatments, enhance patient care and standardise documentation of AE within the clinical datasets.

**Trial registration:**

ClinicalTrials.gov NCT02747264.

**Electronic supplementary material:**

The online version of this article (10.1186/s40814-018-0304-6) contains supplementary material, which is available to authorized users.

## Background

An estimated 17,000 patients are treated annually in the UK with radical radiotherapy (RT) for pelvic cancer [1]. New treatment approaches such as intensity-modulated radiotherapy (IMRT), image-guided radiotherapy (IGRT), fractionated delivery [2] and concomitant chemoradiotherapy (chemoradiotherapy (CRT)) have changed the subjective toxicity profile of radiotherapy (RT). Patients survive longer but suffer acute and long-term pelvic-related AE. Multi-disciplinary follow-up creates difficulty for monitoring and responding to these events during treatment and beyond [3]. In order to support patients and fully understand the effects of new treatments, improved and more timely documentation of acute, intermediate and late AE is essential [4].

Prostate patients with localised cancer have good long-term prognosis but endure the long-term effects of pelvic RT [5]. In both cervical and ano-rectal cancer CRT improves outcomes at the expense of additional chemotherapy specific toxicities and the late bowel, urinary and sexual side effects from RT [6, 7]. Overall, for patients treated with pelvic RT 59% women and 45% men will have long-term gastrointestinal (GI) side effects, e.g. bowel urgency [8]. Long-term genitourinary (GU) side effects (e.g. urinary urgency) are experienced by 49% women and 46% men, and 24% women and 53% men state their ability to have a sexual relationship is affected [8].

Assessment and documentation of RT-related AE is generally inconsistent; therefore, improving the systematic and consistent recording of AE would inform strategies to reduce the impact of AEs on patients, clinicians and the health service [4, 6]. Late effects of pelvic RT only fully develop and affect patients’ months/years post-treatment, when centralised follow-up in specialised RT clinics is often infrequent. A cost-effective model to allow remote measurement of RT-AE would help patients to get appropriate specialist advice and support when late toxicity emerges. Systematic data collection would also allow comparisons and evaluation of the benefits of new RT approaches.

In RT, AE are generally reported by clinicians using the RTOG scale for acute AE and the Late Effects on Normal Tissues–Subjective, Objective, Management and Analytic (LENT-SOMA) [9]. Scale, which has been incorporated into the National Cancer Institute’s (NCI) Common Terminology Criteria for Adverse Events (CTCAE v.3), now superseded by v.4 [10]. However, traditionally clinician-reported AEs are heavily focussed on safety and the rare more severe grades of toxicity.

### Patient-reported outcomes (PROs)

Asking patients to report their own symptoms via patient-reported outcomes (PROs) has proven extremely acceptable to patients in the oncology clinic setting [10–13]. Reviews suggest they improve symptom/function monitoring, physician patient communication, decision-making [14–19], timing and accuracy of symptom reporting [20]. PROs have been increasingly recommended by the United States Food and Drug Administration (FDA) [21] and here in the UK in the 2008 Darzi report [22]. The Department of Health (DOH) subsequently produced guidelines to aid their implementation [23], and we now have some nationwide use of PROs in the NHS [24]. In terms of monitoring toxicity, the CTCAE scale has recently been adapted for patients to self-report (NCI-PRO-CTCAE) [25, 26]. These items have concordance with nurse-evaluated AE [27] and similar items created for self-report correlate with quality of life (QOL) measures [28]. Increasingly, patients are being asked to monitor their own health status and self-manage symptoms. In response to this, we have developed the eRAPID system to improve the detection, and management of AE in cancer patients by providing the means by which patients can report symptoms from home [29, 30].

### Electronic PROs (ePROs)

The use of ePROs in health research has risen exponentially during the past 20 years for a number of conditions including cancer [31, 32]. Patients have shown they can routinely complete PROs electronically, [11] and paper and electronic completions are comparable [33]. Further, RT patients and staff said they would find an internet PRO reporting tool acceptable. Clinicians thought this would improve their consultations with having graphical representation of the PRO data [34]. It is also clear that patients are willing and able to use PROs from home internet or mobile devices [35, 36].

Examples of successful implementation of electronic symptom reporting in oncology clinical practice include PatientViewpoint [37], a flexible PRO platform, the symptom tracking and reporting system (STAR) for patients to report chemotherapy AE [35], and the Tell Us™ [38] system for advanced cancer patients in hospices undergoing palliative care (all in the USA). In Canada, they have developed an interactive online system (ISAAC) [39] and in the UK the ASyMS mobile phone system [40]. Electronic patient-reported outcome systems have proven very acceptable even for patients coping with extreme symptom burden and reduced QOL; indeed, a mean monthly PROM completion rate of 83% at 34 weeks was achieved with patients receiving cancer treatment [41]. In RT, the VisionTree Optimal Care online reporting tool has proven acceptable to patients and increased QOL completion compliance to 90% compared to paper completion of 50% [42].

### eRAPID development

In Leeds, we recently commissioned the development of a web-based questionnaire builder system called QTool (built by X-Lab, a private software company and funded by Macmillan Cancer Support and Cancer Research UK) (www.epocs.leeds.ac.uk). QTool Version1 was used in a large prospective study of cancer survivors [43]; however, the PROs were not viewed by clinicians. Utilising this technology eRAPID is an online system to support the collection and clinical integration of patients’ symptom/AE reports during cancer treatment [30]. Between 2010 and 2013, the eRAPID developmental work was conducted (funded by a National Institute of Health Programme Development Grant RP-DG-1209-10,031). Developed originally for use in systemic treatment, the system enables patients to report AE via PROs [44] and the questionnaire data is integrated into the electronic patient records (EPR) for clinicians to view. Algorithmic questionnaire scoring [44, 45] generates severity dependent management advice to either call the hospital or self-manage symptoms (accessible via a custom build website). Currently, an RCT in systemic therapy is underway recruiting 500 patients [46]. We have now adapted the system for use in upper gastrointestinal surgery and RT.

### Multi-site eRAPID radiotherapy development

Developmental work was conducted to adapt the eRAPID system for RT in two centres (Leeds and The Christie Hospital Manchester) and for patients undergoing pelvic radiotherapy for urological, gastrointestinal and gynaecological cancer. A rigorous systematic approach was adopted according to the criteria for reporting the development and evaluation of complex interventions in healthcare [47] and the Medical Research Council (MRC) guidelines [48].

In this two-centre study, professional and patient care pathways and the role of eRAPID were explored via audit and interviews with staff, patients and relatives [49–51]. Additionally, we identified the AEs associated with urological, gastrointestinal and gynaecological cancers from patient interviews [50] and via systematic reviews of PRO reporting for these groups [52–54]. In a mapping exercise to matching questionnaire items to common adverse events revealed the best questionnaire coverage for adverse events for all tumour groups were the male and female pelvic questionnaires (MPC and FPC) [55]. For a clinical perspective Delphi (consensus methodology) was used with staff to make decisions on the most appropriate items for each AE [56]. This led to the inclusion of additional items from the EPIC (Expanded Prostate Cancer Index) and the EORTC-QLQC-30 and PR 25 (prostate module). In addition, to cover chemotherapy-related AE items were taken from item pool developed for eRAPID (systemic therapy) [44]. See (Additional file 1: Appendix 1) for example of AE items used either as standard, branching (having a prior qualifying question) or as a drop-down (allowing selection of more appropriate options).

The AE questionnaires are scored according to specific algorithms developed in consultation with key staff and patients. Clinically meaningful cut scores for symptom severity were developed through consenus and discussion based methods [57]. The scorning and algorithms allows the generation of severity-dependent management advice for either mild (self-management advice), moderate (self-management and advice to contact the hospital when appropriate) or severe (advice to contact the hospital immediately). The self-management advice for mild level symptoms was developed from local and reputable national resources [58] and uploaded to two designated websites for Leeds and The Christie patients. AE. The online system is now successfully implemented at Leeds Teaching Hospitals NHS Trust (LTHT) and The Christie Hospital Manchester.

### The eRAPID intervention in radiotherapy

The developmental work led to the eRAPID complex intervention [44, 46] consisting of the following components (see Figs. 1 and 2):Patients login to QTool using unique usernames and password and complete the eRAPID symptom questionnaire from home on computers/mobile phones/tablets or using designated kiosks (Leeds). Immediate tailored automated advice, calculated from a series of algorithms, is generated.If severe symptoms are reported, patients are advised to contact the hospital.For mild/moderate problem information about self-managing, these issues are provided via brief instructions in QTool and hyperlinks to more detailed advice on the eRAPID RT patient websites tailored to Leeds and The Christie local information.The patient-reported data is immediately available for staff to review in the individuals’ EPR in Leeds Teaching Hospitals NHS Trust (PPM), The Christie Clinical Web Portal (CWP).Notifications for severe symptom reports are sent directly to staff via email. Clinicians can then login to PPM and CWP and view the patients’ symptom reports and take appropriate action where needed.

**Fig. 1 Fig1:**
[figure not shown]
eRAPID system architecture overview

**Fig. 2 Fig2:**
[figure not shown]
Screenshots of eRAPID intervention Patient login (**a**-**f**) **a** Login eRAPID portal, **b** access eRAPID websites for (QTool) login (Leeds and Manchester), **c** login to online symptom report, **d** complete symptom report, **e** recieve advice to manage low-level symptoms, **f** login to online symptom report. Clinician view of symptom reports in electronic patient record (EPR) (**g** & **h**) **g** symptom reports in EPR (tabular view), **h** symptom reports in EPR (grapical view)

### Aims and objectives

We aimed to conduct the initial pilot study of the eRAPID system in radiotherapy from the perspective of cancer patients and health professionals. The objectives are to establish feasibility and determine effect sizes of the potential benefits of the intervention for a future RCT.

The specific aims are to:Establish recruitment and attrition ratesEstablish adherence to symptom reporting and record the number of calls made to the hospital by patientsTest the integrity of the study protocol and data collection formsTest the integrity of information systems designed to collect and collate the dataAid selection of the most appropriate primary outcome measure and determine effect sizeRefine the intervention by exploring patient and staff views.

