### Randomisation

Participants are randomised with 1:1 allocation to intervention and control groups, performed centrally at the University of Leeds Clinical Trials Research Unit (CTRU) using the 24-h telephone system. Patients randomised to the intervention arm receive training in using the eRAPID system.

Patients are already stratified by cancer centre (Leeds or Manchester) and will be further stratified by cancer site, e.g. prostate or cancer requiring chemo RT (cervix, anal, rectal, vaginal, endometrial and vulval). A diagrammatic representation of the stratification factors is presented in Fig. 4.

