### Sample size and recruitment rate

Thirty patients per arm for each treatment type will provide valuable information on outcomes [60] (Tables 1 and 2) Allowing for 30% overall attrition, we aim to recruit a minimum of 42 patients per-arm (*n* = 84 for each treatment type) at a rate of around 15 patients per month for approximately 15 months giving an overall total of 168 patients, with a 24-week follow-up.

**Table 1 Tab1:** eRAPID RT study questionnaires and Case Report Forms (CRFs): researcher completed

Questionnaire/CRF	Time point for completion
Eligibility checklist	Baseline
Comorbidity form	End of study
Consent form	Baseline
Registration/randomisation form	Baseline
Baseline: clinical data form	End of study
Clinical process measures Number of hospital contacts Number of alerts and hospital admissions Readmissions (with reasons) Clinician records of CTCAE and RTOG Changes to supportive medications and RT and/or chemotherapy dose changes Contacts with GP/community services Safety monitoring acute admissions, cumulative deaths	Collected during a course of RT treatment and if appropriate chemotherapy cycle (from hospital records and via brief patient survey at routine clinic appointments for interim assessment of clinical contacts)
IT system functioning Telephone log of phone calls from patients Record of unscheduled server down time	Throughout the duration of the study
Death and withdrawal form	At point of death/withdrawal

**Table 2 Tab2:** eRAPID RT study questionnaires and Case Report Forms (CRFs): participant completed

Questionnaire/CRF	Description of time points for completion	Baseline	3 weeks	6 weeks	9 weeks	12 weeks	18 weeks	24 weeks
Consent form	Baseline	X						
Baseline: patient sociodemographic data form	Baseline	X						
Baseline: computer usage questionnaire	Baseline	X						
Patient-reported eRAPID symptom questionnaire (eRAPID intervention arm only)	Within 24 h of study entry and weekly during treatment and 6 weeks afterwards (12 weeks total). Then at 18 and 24 weeks.	X weekly	X weekly	X weekly	X weekly	X weekly	X (except rectal)	X (except rectal)
Patient Outcome Measures FACT-G EORTC-QLQ-C30 EQ-5D-5 L	Baseline, 6, 12 and 24 weeks	X		X		X		X
Self-efficacy, Lorig 6-item	Baseline and 12 weeks	X				X		
Patient Activation Measure (PAM)	Baseline and 12 weeks	X				X		
Use of resources form	6, 12 and 24 weeks			X		X		X
System Usability Scale	24 weeks (eRAPID intervention arm only)							X

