### Selection of patient outcome measures

Patient outcome measures (see Table 2) will be summarised at each time point, and 95% confidence intervals constructed for the differences between treatment arms. In addition, the number of questionnaires completed and the extent of missing data will be presented. To aid selection for a future RCT, any ceiling and/or floor effects from the questionnaires will be noted.

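### The pilot aims to determine effect sizes for a future RCT, but its size only allows them to be estimated within about ±0.36 SD (pooled) or ±0.52 SD (per treatment type)

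*Protocol article*

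**What the plan says.** Aims and objectives gives the purpose as: "The objectives are to establish feasibility and determine effect sizes of the potential benefits of the intervention for a future RCT". One item in its list of specific aims joins the choice of a primary outcome to the effect size. The abstract's Discussion repeats the pairing, "determine effect sizes and aid selection of the primary outcome measure for a future RCT", and so does the article's closing Discussion.

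The basis for the size is in the abstract's Methods: "We aim to recruit 168 patients following recommendations for sample size estimates for pilot studies". Sample size and recruitment rate adds: "Thirty patients per arm for each treatment type will provide valuable information on outcomes", and then "Allowing for 30% overall attrition, we aim to recruit a minimum of 42 patients per-arm", "giving an overall total of 168 patients, with a 24-week follow-up". No SD, target difference, power or interval width is given.

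Selection of patient outcome measures plans summaries at each time point with "95% confidence intervals constructed for the differences between treatment arms", together with numbers completed, missing data, and floor and ceiling effects. Only the floor and ceiling effects are tied explicitly to selecting a measure for the RCT. The section does not say whether the intervals are pooled over treatment types or given for each.

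**The concern.** A sample of this size is suited to learning about recruitment, completion, attrition and variability. An effect size is a harder quantity, and the article claims to determine it in three places without stating how precisely it would be known. If RCT designers took the claim at face value, they could size the RCT on a figure that is compatible with anything from no effect to a large one.

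The second issue is that outcome selection and effect size form one aim on one dataset. If the measure were chosen because its observed difference was largest, that difference would tend to overstate the true effect, and an RCT sized on it would be under-powered. This depends on how the choice is made, which the article does not fix.

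**Working it through.** **Inputs from the protocol article.** There are 30 evaluable patients per arm per treatment type, 30% attrition, 42 recruited per arm per type, two treatment types and 168 in total (Sample size and recruitment rate). Allocation is 1:1 (Randomisation). Intervals are 95% (Selection of patient outcome measures). Outcomes are put on a standardised scale, SD = 1, because the article gives no SD.

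**The plan's own figure.** 42 × 2 arms × 2 types = 168, as stated. 30/0.7 = 42.86, which rounds up to 43 against the stated 42; conversely 42 × 0.7 = 29.4. The difference is trivial and is not raised as an error.

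**Precision of a between-arm difference.** Half-width = t(0.975, 2n − 2) × √(2/n).

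- One treatment type, n = 30 per arm: 2.002 × √(2/30) = 2.002 × 0.2582 = 0.517 SD.
- Both types pooled, n = 60 per arm: 1.980 × √(2/60) = 1.980 × 0.1826 = 0.362 SD.

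An observed difference of 0.3 SD would therefore have a 95% interval of about −0.22 to 0.82 SD in one type and −0.06 to 0.66 SD pooled. At 80% power and two-sided 5%, a true effect of 0.3 SD needs 175 per arm and one of 0.2 SD needs 393 per arm, so the pilot interval spans very different RCTs.

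Adjustment for baseline would help. Multiplying the normal-approximation half-width, 1.96 × √(2/n), by √(1 − r²), with an assumed baseline correlation r of 0.5 to 0.7, gives 0.44 to 0.36 SD at 30 per arm and 0.31 to 0.26 SD at 60 per arm.

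**Illustration of selection, only if the largest observed effect is picked.** Assumptions, none of them in the article: every candidate has a true effect of 0.2 SD, the estimates are equally correlated, and the RCT is sized for 90% power at two-sided 5%. The mean of the largest observed effect comes from 200,000 simulated pilots per setting. The RCT size per arm is 2(1.96 + 1.2816)²/d² = 21.015/d², where d is that mean. True power is Φ(0.2 × √(n/2) − 1.96).

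| Pilot n per arm | Candidates | Correlation | Mean largest effect | RCT n per arm | True power |
|---|---|---|---|---|---|
| 60 | 3 | 0.5 | 0.310 | 219 | 55% |
| 60 | 5 | 0.5 | 0.351 | 171 | 46% |
| 30 | 3 | 0.5 | 0.355 | 167 | 45% |
| 30 | 5 | 0.5 | 0.412 | 124 | 35% |

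For comparison, 0.2 SD at 90% power needs 21.015/0.04, or 526 per arm. Varying the correlation from 0.3 to 0.7 with three to five candidates gives true power of 41% to 62% at 60 per arm and 30% to 53% at 30 per arm.

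The range of three to five candidates reflects the article. The Patient Outcome Measures row of Table 2 names three instruments. Table 2 also lists self-efficacy and patient activation without marking them as intervention-only, but the eRAPID intervention section describes them as completed by the intervention arm, so their status as between-arm candidates is unclear.

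If the choice ignores the observed difference, this bias is about zero.

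**The case against.** The sample size is openly a pilot convention, and the planned analysis is already descriptive: intervals for arm differences, completion, missing data, and floor and ceiling effects. A designer who sees those intervals will see the imprecision. The article does not say that the RCT will be sized on the pilot's point estimate, and it contains no rule that stops the programme on a null difference. Pooling and baseline adjustment narrow the interval. A full statistical analysis plan exists but is not shown, so detail on summaries and selection cannot be called missing.

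Most of this is fair, and it limits the point to the stated aim. It does not remove it: the claim to determine effect sizes is made positively in the article, and even the pooled, baseline-adjusted interval (0.26 to 0.31 SD either side) is too wide to support it.

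A reader might go further and infer that the chosen measure's effect will necessarily be inflated. The documents do not support that. No section selects the outcome by its observed difference, and the only criterion tied explicitly to selection, floor and ceiling effects, does not by itself produce such a bias. What stands is weaker: the arm differences are reported in the section headed as concerning selection, one aim joins selection to effect size, and nothing excludes using the one for the other.

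**Conclusion.** The concern holds as a mismatch between a stated aim and the design. The pilot can estimate between-arm effects with a 95% half-width of about 0.52 SD per treatment type or 0.36 SD pooled, before baseline adjustment. It cannot determine them. These figures rest only on the article's evaluable numbers and a comparison of two means in SD units.

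Inflation of the chosen measure's effect is a conditional risk. The power figures apply only if the largest observed effect is picked, and they depend on the assumed common true effect of 0.2 SD, the correlation, the number of candidates and the 90% target. They show what could follow, not what the plan prescribes. A restatement should be made because it is cheap and changes what the RCT may take from the pilot.

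**What to change.** In Aims and objectives, the abstract's Discussion and the article's closing Discussion, replace the claim to determine effect sizes with an aim to estimate the SD, the baseline-to-follow-up correlation and the completion of each measure, and between-arm differences with 95% confidence intervals.

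In Selection of patient outcome measures, add two statements:

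- The RCT's primary outcome will be chosen on relevance, completeness, and floor and ceiling effects, and not on the size of the observed difference.
- The RCT's target difference will come from a clinically important difference, with the pilot supplying the SD, the correlation and the attrition rate.

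Recruitment, randomisation, data collection and the between-arm comparisons already planned stay as they are; SDs and baseline correlations come from data already collected. The cost is a more modest stated aim.
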